##### - *Blood samples collection procedures*

All subjects are tested for 25OHD concentration at W0, and actually included subjects are also tested at W12 and W24. Blood sampling are done by a clinical research nurse at each consultation. Serum 25OHD concentration is then measured with the DiaSorin radioimmunoassay (RIA) kit (DiaSorin, Stillwater, MN, USA) locally at the University Hospital at Angers, France, to homogenize the measuring technique. The RIA DiaSorin kit is the most used kit for such studies and recognizes both D_2 _and D_3_. With this method, there is no interference of lipids, which is often observed in other non chromatographic assays of 25OHD. Additionally, this method correlates with the reference method (high-performance liquid chromatography with mass spectrometry [HPLC-MS]). The intra- and interassay precisions are respectively 5.2% and 11.3% (range in normal adults aged 20-60 yr, 30-125 ng/mL).

##### - Safety parameters

The safety assessment parameters are:

- Clinical: delirium, somnolence, asthenia, vertigo, headache, epilepsy, nausea and vomiting, heart failure, lumbar or right hypochondre pain in the case of biliary or renal colics revealing calcic lithiasis (objectivized with echography in the case of clinical suspicion), thrombosis (objectivized with doppler in the case of clinical suspicion);

- Biological: serum calcium concentration. The serum concentration of calcium is measured at baseline assessment, then at W12 and W24 to monitor the occurrence of hypercalcemia > 2,65 mmol/L [32]. The occurrence of hypercalcemia leads to double-blind termination and premature withdrawal from the study, stops the vitamin D supplementation and potential calcium supplements, and triggers further complementary non-specific examinations to find the cause of hypercalcemia for which vitamin D intake could not be held responsible at first [16].

### Statistics

#### Sample Size Calculation

The trial aims to recruit 120 patients over a period of 52 weeks. According to previous literature, we estimate that the change in ADAS-cog score after 24 weeks in patients receiving memantine will be 1.25 ± 5 points on average [8]. In addition, it is usually considered in clinical trials among AD patients that the minimum clinically relevant change in ADAS-cog score is at least 3 points [40].

Thus, assuming a reference value of 1 and a variance of 25 (standard deviation estimated at 5), a two-sided test with an alpha risk of 5%, and a power (1 - beta) of 99%, the sample size to detect a 3-point difference in change from baseline in the ADAS-cog between the 'Intervention' group and the 'Placebo' group, is 52 subjects per group (total 104 subjects).

Taking into account the loss to follow-up (estimated at 15%), it is necessary to include a total of 120 subjects (60 per group). This sample size has also adequate power (i.e., 90%) to detect a smaller difference in ADAS-cog score (i.e., 2 points). The sample size calculation also assumes accounting for up to 12 covariables anticipating multivariate analyses, including the change in comorbid conditions possibly due to vitamin D supplementation [51] with subsequent indirect cognitive benefits (using the Cumulative Illness Rating Scale for Geriatrics [CIRS-G] score) [52], the education level [1], the season tested [16], and the serum concentrations of parathyroid hormone (PTH) and calcium [53].

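### The sample size section claims 99% power at 3 points and 90% at 2 points; 52 per group gives about 86% and 52%

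*Protocol article*

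**What the plan says.** All of the relevant text is in the protocol article, Statistics, Sample Size Calculation.

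- **Variability:** the expected result on memantine is that "the change in ADAS-cog score after 24 weeks in patients receiving memantine will be 1.25 ± 5 points on average". The calculation itself proceeds "assuming a reference value of 1 and a variance of 25 (standard deviation estimated at 5").
- **Test and contrast:** "a two-sided test with an alpha risk of 5"%, for a "3-point difference in change from baseline in the ADAS-cog between the 'Intervention' group and the 'Placebo' group".
- **Power and size:** "a power (1 - beta) of 99%, the sample size to detect a 3-point difference in change from baseline in the ADAS-cog" between the two arms "is 52 subjects per group (total 104 subjects").
- **Loss:** "Taking into account the loss to follow-up (estimated at 15%), it is necessary to include a total of 120 subjects (60 per group").
- **Smaller effect:** "This sample size has also adequate power (i.e., 90%) to detect a smaller difference in ADAS-cog score (i.e., 2 points").

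The next section, Analyses, plans an independent-samples t-test or Mann-Whitney test on the changes, and an analysis of covariance. The comparison being powered is therefore one of two independent groups.

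**The concern.** A 3-point difference with an SD of 5 is a standardised difference of 0.6. Having 99% power for an effect of that size with about 50 patients per arm is implausible on sight, and 90% power at a standardised difference of 0.4 is more so.

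These are the power statements for the primary outcome. If they are wrong, a null result will be over-read: as near-exclusion of a 3-point effect, which the protocol treats as clinically relevant, and as good evidence against a 2-point effect. The data monitoring committee, which sees the between-treatment difference on the primary outcome and can recommend closure, would also be working from wrong design properties.

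**Working it through.** **Inputs**, all from Sample Size Calculation: difference 3 (then 2) points between groups; SD of change 5 (variance 25); two-sided alpha 5%, so z = 1.960; power 99%, so z = 2.326 (90%: z = 1.282); 52 per group evaluable; 15% loss; 120 enrolled at 1:1.

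**1. Reproducing the stated 52.** The one-sample formula against a fixed value gives

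n = (1.960 + 2.326)² × 25 / 3² = 51.03, rounded up to **52**.

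This matches. The same inputs in the two-group formula give

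n per group = 2 × (1.960 + 2.326)² × 25 / 3² = 102.07, so **103 per group**, or 104 with the exact t calculation.

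A one-sided two-group test at 99% would need 88 per group, so a change of sidedness does not explain 52 either.

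**2. Power the design actually has** (two-sample t-test, noncentral t, SD 5, two-sided 5%):

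| Evaluable per group | Basis | 3 points | 2 points |
|---|---|---|---|
| 51 | 120 × 0.85 = 102 | 85.1% | 51.6% |
| 52 | the stated evaluable number | 85.8% | 52.4% |
| 60 | all enrolled, no loss | 90.3% | 58.4% |

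The normal approximation gives nearly the same values: 86.4% and 53.2% at 52 per group, 90.8% and 59.1% at 60.

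**3. The 2-point claim.** For 90% power at 2 points,

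n per group = 2 × (1.960 + 1.282)² × 25 / 2² ≈ 131.3, so 132 per group, or 133 by exact t.

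The claim also fails under the one-sample formula that yields 52. There the power at 2 points is about 82% with n = 52 and about 87% with n = 60.

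**4. Difference detectable with 90% power** (exact t): 3.24 points at 51 per group and 3.21 at 52, so about 3.2.

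**5. What would make the claims true.**

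- 99% at 3 points with 52 per group needs an SD of about 3.57. Covariates would have to explain 1 − (3.57/5)² ≈ 49% of the variance of the change.
- 90% at 2 points needs an SD of about 3.15 with 52 per group or 3.38 with 60. That is about 60% or 54% of the variance explained.

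**6. Loss.** 104 × 1.15 = 119.6 gives the stated 120. The number needed to retain 104 is 104 / 0.85 = 122.4, so 123. With 120 enrolled and 15% lost, 102 remain. This costs under one percentage point of power at either difference (52 against 51 per group in the table).

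**The case against.** The strongest counter-argument is that the primary target is not underpowered in the usual sense. Power at 3 points is about 85% after loss, above the customary 80%, and nothing in the conduct of the trial has to change. That is correct. It limits the consequence, but it does not make the stated figures right.

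Several narrower objections also have some force.

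- **Which n the 2-point claim refers to.** The sentence follows the figure of 60 per group, so 60 may be meant. It would then be unfair to argue that the two power claims contradict each other at one fixed n. But at 60 per group the power is 58.4%, and the 90% claim still fails.
- **The covariate sentence.** The text says that up to 12 covariates were allowed for. This could mean a subjects-per-variable rule (120 / 12 = 10) rather than a variance reduction. The article does not say, so I do not count the sentence as an error. It does not rescue the power figures either: no explained variance is stated, and 52 follows from an SD of 5 with no covariate term.
- **The origin of 52.** The one-sample formula fits both the number and the mention of a reference value of 1, but that is an inference. The reference value could be a rounded control-arm mean. The conclusion does not depend on the diagnosis.
- **The loss inflation.** It is a small slip and would not merit action on its own.

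**Conclusion.** The concern holds, and the power statements should be corrected. On the document's own inputs (SD 5, two-sided 5%, two independent groups), 52 per group gives about 86% power at 3 points instead of 99%, and about 52% at 2 points instead of 90%. On the most favourable reading, 60 per group with no loss, the figures are 90% and 58%.

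The risk of missing a true effect at 52 per group is about 14% at 3 points, against the stated 1%. At 2 points it is about 48%, against the stated 10%. The 2-point claim is the more serious error, because it would support a negative conclusion that the trial cannot deliver.

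The result rests on an SD of 5 for the unadjusted 24-week change. Adjustment for baseline or other covariates would raise power, but reaching the stated figures would require roughly half or more of the variance to be explained, which the document does not assume. A Mann-Whitney test with normal data would lower power slightly, to about 84% and 51% at 52 per group.

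**What to change.** Keep 120 patients and replace the power statements in Sample Size Calculation with wording such as:

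> With 120 patients randomised and 15% loss to follow-up (51 evaluable per group), an SD of 5 and a two-sided 5% test, power is about 85% for a 3-point and about 52% for a 2-point between-group difference in change. The difference detectable with 90% power is about 3.2 points.

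Delete the 99% claim, the claim of 90% at 2 points, and the reference value of 1, which has no role in a two-group calculation. Either say what allowing for 12 covariates means in the calculation or remove that statement.

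An analysis of covariance is already planned. Naming the baseline ADAS-cog score as a covariate in the primary comparison would be a sensible way to recover some precision without more patients, though the correction does not depend on it.

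The cost is a change of wording and a less favourable stated power. No extra patients are needed.

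### At the plan's own 15% loss, 120 enrolled leave 102 patients (51 per group), not the stated 104: a minor inconsistency, secondary to the fault in the 52 per group itself

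*Protocol article*

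**What the plan says.** All the figures are in one place, the protocol article's Sample Size Calculation section.

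- **Target difference:** the calculation is "to detect a 3-point difference in change from baseline in the ADAS-cog between the 'Intervention' group and the 'Placebo' group".
- **Variability:** it assumes "a variance of 25 (standard deviation estimated at 5").
- **Error rates:** it assumes "a two-sided test with an alpha risk of 5%, and a power (1 - beta) of 99"%.
- **Number needed:** the result "is 52 subjects per group (total 104 subjects").
- **Loss allowance and enrolment:** "Taking into account the loss to follow-up (estimated at 15%), it is necessary to include a total of 120 subjects (60 per group").

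The section then claims 90% power for a 2-point difference with the same sample size. It does not say by what formula the loss allowance was applied.

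**The concern.** The section presents 120 as the enrolment that protects 104 patients against a 15% loss. Patients are lost from those enrolled, so the enrolment has to be the needed number divided by the retained fraction, 0.85. Adding 15% to the needed number gives too small a figure.

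What is at stake is modest. The enrolment does not deliver the plan's own number at the plan's own loss rate. The practical consequence is that any power statement for this trial should be made at 51 per group, not at 52 or 60.

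**Working it through.** **Inputs**, all from Sample Size Calculation: difference 3 points (and 2 points for the second power claim), SD 5, two-sided alpha 5%, power 99%, number needed 52 per group (104), loss 15%, enrolment 60 per group (120).

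**1. Reproducing the stated 120.**
- 104 × 1.15 = 119.6, which rounds to 120.
- 52 × 1.15 = 59.8, which rounds to 60.

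The plan's figure is reproduced by adding 15%. That this was the method is an inference from the match.

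**2. What 120 leaves after a 15% loss.**
- 120 × 0.85 = 102, two below 104.
- 60 × 0.85 = 51, one below 52.

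**3. What keeping 104 would need.**
- In total: 104/0.85 = 122.4, so 123.
- Per group: 52/0.85 = 61.2, so 62, or 124 with equal groups.

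The stated enrolment is therefore 3 to 4 patients lower.

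**4. The loss that 120 can absorb.** 1 − 104/120 = 16/120 = 13.3%.

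**5. Cost in power.** Two-sample t-test, equal groups, noncentrality = difference / (SD × √(2/n)), with 2n − 2 degrees of freedom:

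| n per group | Noncentrality, 3 points | Power, 3 points | Noncentrality, 2 points | Power, 2 points |
|---|---|---|---|---|
| 52 | 0.6 × √26 = 3.06 | 85.8% | 0.4 × √26 = 2.04 | 52.4% |
| 51 | 0.6 × √25.5 = 3.03 | 85.1% | 0.4 × √25.5 = 2.02 | 51.6% |

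Losing one patient per group costs 0.7 percentage points for 3 points and 0.8 for 2 points.

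**6. Is 52 per group a valid benchmark?** For two independent groups:
- n = 2 × SD² × (1.960 + 2.326)² / 3² = 2 × 25 × 18.37 / 9 = 102.07, so 103 per group.
- By the t-test, 103 per group falls just short of 99% and 104 exceeds it (99.05%).
- Half of 102.07 is 51.03, which rounds up to 52. So 52 is what the formula gives without the factor 2 for two groups. This too is an inference from the number.
- The 90% claim for 2 points would need 132 per group. Even 60 per group with no loss gives about 58% (t-test).

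Step 6 is a different and much larger error than steps 1 to 4. Raising enrolment to 124 would not repair it: 62 per group with no loss at all gives about 91% for 3 points (t-test).

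**The case against.** **The discrepancy is trivial.** Two patients and less than one percentage point of power change no design decision. The 15% is itself an estimate, and the gap between 15% and 13.3% is smaller than any realistic uncertainty about it. This stands as an argument about weight. It does not make the three printed figures consistent.

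**The benchmark is wrong anyway.** Being two short of 104 means little when the stated inputs call for about 206. This stands, and it limits the fix: the correction must not preserve 104 as a valid target. The loss allowance is still a separate step. Applied to a corrected base it would go wrong on a larger scale: 206 × 1.15 = 236.9, so 237, against 206/0.85 = 242.4, so 243.

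**The mechanism is not stated.** A reader might conclude that the plan multiplied by 1.15. The match with 119.6 is close, but no formula is given and 120 is also a round recruitment target. The documents support only that 120 does not retain 104 at a 15% loss, and the point does not depend on how 120 arose.

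**Intent-to-treat may retain patients.** A reader might infer that exactly 102 patients will be analysed. The documents do not support that. The trial is described as intent-to-treat, there is a week-12 assessment, and patients who stop medication are encouraged to remain in follow-up. How patients without week-24 data are handled is commonly left to an analysis plan, which is not shown. The figure of 102 is a planning count of patients with week-24 data. It is the right comparison here because the section itself sets aside an allowance for those lost.

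**Conclusion.** The point holds as a minor arithmetic inconsistency. At a 15% loss, 120 enrolled leave 102 patients with week-24 data (51 per group), not 104 (52 per group). The shortfall is two patients with data, equivalent to 3 or 4 enrolled, and costs 0.7 to 0.8 percentage points of power.

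It is secondary to the fault in the base figure: 52 per group gives about 86% power for 3 points, not 99%. A reader might infer that the loss allowance is what leaves the trial short of its stated power, or that enrolling 124 would restore it. Neither follows, because nearly all of the gap comes from the 52.

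The result assumes that the loss is exactly 15% and equal in both groups, and that those lost contribute no week-24 value. The power figures further assume SD 5 and an unadjusted two-sided 5% t-test, which is one of the tests named under Analyses. Covariate adjustment could change them, but the article gives no correlation from which to calculate by how much.

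**What to change.** Keep the enrolment at 120 and restate what it delivers. For example: *With 60 patients enrolled per group and a 15% loss to follow-up, about 51 per group are expected to have week-24 data. With SD 5 and a two-sided 5% t-test, this gives about 85% power for a 3-point difference and about 52% for a 2-point difference.*

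This replaces both the 99% and the 90% power statements. It should not present 104 as the number needed for 99% power, and it need not mention 104 at all.

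The cost is a short change to one paragraph, with no effect on enrolment or conduct. The downside is that the stated figures become less favourable, most visibly for the 2-point difference.

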#### Analyses

The effect of vitamin D supplementation compared to placebo will be determined using evaluation criteria, which are the changes in cognitive, functional and physical scores between W0 and W12 and between W0 and W24, using independent samples t-test or Mann-Whitney U test; and the between-group comparisons of changes in cognitive, functional and physical scores between W0 and W12, and between W0 and W24, using an analysis of covariance.

Any exploratory analyses here will use multivariate logistic and proportional hazards regression. In addition, the stratification criterion for randomization (i.e., the nature of dementia: AD or RD) will be also taken into account in the multivariate models. Excessive subgroup analyses can give rise to misleading results and therefore all subgroup investigations will be interpreted cautiously. In particular, subgroup analysis will be conducted depending on the severity of hypovitaminosis D at the beginning of the study (i.e., serum 25OHD concentration below or above 10 ng/mL) and on the severity of dementia at the beginning of the study (i.e., MMSE score below or above 15). Finally, special attention will be paid to participants that, while having hypovitaminosis D at the beginning, did not show high levels of PTH, to determine whether this group differentiates of the PTH responders in terms of therapeutic benefits.

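### The sample size is said to account for up to 12 covariables, but the stated figures contain no allowance for them; the cost to the ANCOVA is at most about 5 points of power

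*Protocol article*

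**What the plan says.** All figures come from the Sample Size Calculation section of the protocol article. The inputs are given as "assuming a reference value of 1 and a variance of 25 (standard deviation estimated at 5" points, with "a two-sided test with an alpha risk of 5%, and a power (1 - beta) of 99" per cent. The result, described as "the sample size to detect a 3-point difference in change from baseline in the ADAS-cog", "is 52 subjects per group (total 104 subjects" in all. The next step is "Taking into account the loss to follow-up (estimated at 15" per cent, after which "it is necessary to include a total of 120 subjects (60 per group" in all.

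The section then adds: "The sample size calculation also assumes accounting for up to 12 covariables anticipating multivariate analyses". It names five such variables: change in comorbidity (CIRS-G), education, season, and serum PTH and calcium. It gives no assumed R², variance inflation or patients-per-variable rule.

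The Analyses section plans t-tests or Mann-Whitney tests and an analysis of covariance for the score changes. It also says: "Any exploratory analyses here will use multivariate logistic and proportional hazards regression". The randomisation stratum (AD or related disorders) is to enter the multivariate models as well, and could be a thirteenth covariate.

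**The concern.** The article attributes a property to its calculation. If the printed inputs already produce the printed sizes, nothing is left that could account for 12 covariables, and the sentence is wrong as a description of how 120 was reached.

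Three things are at stake:

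- An analyst may take the sentence as licence to fit 12 covariates, plus treatment and stratum, and believe that the stated power still applies.
- The sentence refers to multivariate analyses in general. The exploratory ones are event-type models, where the number of events matters and not the number of patients.
- One named covariate is a change after randomisation which the article itself says vitamin D may bring about. Adjusting for such a variable can bias the treatment effect at any sample size.

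**Working it through.** **Inputs from Sample Size Calculation.** Difference 3; SD 5 (variance 25); two-sided alpha 5% (z = 1.960); power 99% (z = 2.326); 52 per group; loss 15%; total 120.

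**Step 1. Reproduce the plan's figures.**

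- Per group: (1.960 + 2.326)² × 25/9 = 51.03, rounded up to 52.
- Total: 104 × 1.15 = 119.6, rounded to 120.

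Both stated sizes are reached with no covariate term. There is no surplus in the second step either: dividing by the retained share gives 104/0.85 = 122.4, or 123.

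**Step 2. Base power without covariates.** The formula in step 1 is the one-sample form. Comparing two group means needs a factor 2:

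- 2 × 51.03 = 102.07, so 103 per group (206 in total) for 99% power.

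Analysable patients: 120 × 0.85 = 102, or 51 per group.

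- Standard error: 5 × √(2/51) = 0.990. Ratio: 3/0.990 = 3.030.
- Power: 85.8% by the normal approximation, 85.1% by the t distribution.

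**Step 3. ANCOVA with 12 covariates, N = 102.**

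- Residual degrees of freedom: 102 − 2 − 12 = 88.
- Expected variance inflation from chance imbalance in the covariates: (N − 3)/(N − q − 3) = 99/87 = 1.138.
- Standard error relative to unadjusted: √(1.138 × (1 − R²)).

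R² is the share of outcome variance that the covariates explain. The article does not give it, so a range is assumed.

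| R² (assumed) | SE ratio | Power for 3 points |
|---|---|---|
| 0 | 1.067 | 80.2% |
| 0.10 | 1.012 | 84.2% |
| 0.12 | 1.001 | 85.0% |
| 0.20 | 0.954 | 88.1% |
| 0.30 | 0.892 | 91.9% |

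Break-even is at R² = 1 − 87/99 = 0.12. A simulation of 20,000 trials gave power 79.6% and type I error 4.9% at R² = 0, and 91.8% and 5.1% at R² = 0.30. A thirteenth covariate changes the two ends to 79.7% and 91.6%. Recovering the unadjusted power at R² = 0 would take about 116 analysable patients instead of 102.

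**Step 4. Event-type models.** The article gives no event definition or rate, so event shares are assumed.

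| Event share (assumed) | Events among 102 | Events per covariate (12) |
|---|---|---|
| 20% | 20.4 | 1.7 |
| 30% | 30.6 | 2.6 |
| 50% | 51.0 | 4.3 |

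**The case against.** Leaving covariates out of a sample size calculation is no error in itself. A two-sample calculation is conservative when the covariates are prognostic, and step 3 shows a gain in power once R² exceeds about 0.12. That stands. The fault is the statement that an allowance was made.

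Twelve is a ceiling and only five variables are named. That also stands, and it makes the worst case less likely.

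The logistic and hazards models are confined to exploratory work, with no event defined and no statement that all 12 covariates would enter each model. So thin events are a caution for any such model and not a measured defect of the plan. Figures for an exaggerated odds ratio would need an endpoint that the article does not contain.

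Three stronger readings are tempting, and the article does not support them:

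- **That 102 patients cannot carry 12 covariates.** For the ANCOVA they can: 88 residual degrees of freedom remain and the type I error holds.
- **That 12 comes from a rule of ten patients per variable.** The arithmetic fits (120/12 = 10, against 102/12 = 8.5 analysable), but the article states no such rule, and falling below it would prove little for a linear model.
- **That covariates explain the shortfall from 99%.** They do not. The missing factor 2 brings power to about 85% before any covariate is added.

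**Conclusion.** The point holds in a limited form. The claimed allowance for 12 covariables is absent from the calculation; this rests only on the article's own figures.

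Its effect on the adjusted analysis of ADAS-cog change is at most about 5 points of power (85.1% to 80.2%), and it becomes a gain if the covariates explain more than about 12% of the variance. This assumes 15% loss, SD 5, and R² between 0 and 0.30. The fall from the stated 99% to about 85% is a separate and larger error in the base formula.

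Twelve covariates would be too many for the exploratory event-type models at event shares of 20% to 50%, which are assumed. The named change in comorbidity is unsuitable as an adjustment variable whatever the sample size. PTH and calcium share that problem only if measured after baseline, and the sample size section does not state their timing.

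**What to change.** - Replace the sentence with: *no allowance for covariates was made in the calculation*. In the same edit, restate the power with the two-group formula: about 85% for 3 points with 102 analysable patients.
- Prespecify a short ANCOVA set of baseline-only variables, in the statistical analysis plan if it is not already there: baseline score, AD/RD stratum, education, season at inclusion, and baseline PTH and calcium if wanted. Leave out the post-randomisation change in comorbidity. The exact number is a judgement; the ANCOVA does not force a particular cap.
- In any logistic or proportional hazards model, limit the number of covariates by the number of events.

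The cost is a change of wording and a shorter covariate list. Some secondary covariates will be left out of the models. This fix does not call for a change in recruitment.

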**Methods:**

The AD-IDEA Trial is a unicentre, double-blind, randomized, placebo-controlled, intent-to-treat, superiority trial. Patients aged 60 years and older presenting with moderate ADRD (i.e., Mini-Mental State Examination [MMSE] score between 10-20), hypovitaminosis D (i.e., serum 25-hydroxyvitamin D [25OHD] < 30 ng/mL), normocalcemia (i.e., serum calcium < 2.65 mmol/L) and receiving no antidementia treatment at time of inclusion are being recruited. All participants receive memantine 20 mg once daily -titrated in 5 mg increments over 4 weeks- and each one is randomized to one of the two treatment options: either cholecalciferol (one 100,000 IU drinking vial every 4 weeks) or placebo (administered at the same pace). One hundred and twenty participants are being recruited and treatment continues for 24 weeks. Primary outcome measure is change in cognitive performance using Alzheimer's Disease Assessment Scale-cognition score. Secondary outcomes are changes in other cognitive scores (MMSE, Frontal Assessment Battery, Trail Making Test parts A and B), change in functional performance (Activities of Daily Living scale, and 4-item Instrumental Activities of Daily Living scale), posture and gait (Timed Up & Go, Five Time Sit-to-Stand, spatio-temporal analysis of walking), as well as the between-groups comparison of compliance to treatment and tolerance. These outcomes are assessed at baseline, 12 and 24 weeks, together with the serum concentrations of 25OHD, calcium and parathyroid hormone.

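### The listed covariables include change in comorbidity (CIRS-G), which the protocol itself describes as a possible effect of vitamin D, so an adjusted efficacy model containing it would not estimate the total treatment effect

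*Protocol article*

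**What the plan says.** The primary objective is the effect of vitamin D3 versus placebo, after 24 weeks, on cognitive performance in patients who all receive memantine. The Design section calls the trial randomised and intent-to-treat.

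The Sample Size Calculation section allows for up to 12 covariables in multivariate analyses and names some of them, "including the change in comorbid conditions possibly due to vitamin D supplementation [51] with subsequent indirect cognitive benefits", to be scored with CIRS-G. It then adds education level and season, "and the serum concentrations of parathyroid hormone (PTH) and calcium". The last two carry no time point. The abstract says that the outcomes are assessed at baseline, 12 and 24 weeks, "together with the serum concentrations of 25OHD, calcium and parathyroid hormone", and Table 1 agrees.

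The Analyses section plans an independent-samples t-test or Mann-Whitney test on changes in score. It also plans between-group comparisons of changes to week 12 "and between W0 and W24, using an analysis of covariance". It lists no covariates for the ANCOVA, says that the AD/RD stratum enters the multivariate models, and does not say which analysis is primary.

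**The concern.** The sentence on comorbidity describes a causal chain: vitamin D may change comorbid conditions, and that change may benefit cognition. A variable in the middle of that chain is a mediator. The primary objective asks for the total effect, which includes any benefit that arrives through better general health. Adjusting for the change in CIRS-G takes that part out.

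There is a second problem. Comorbidity change is not randomised. Patients whose general health worsens may also decline cognitively for reasons that nobody measured. Conditioning on a consequence of treatment that shares such causes with the outcome opens a non-causal association between treatment and outcome, and randomisation no longer protects the adjusted contrast. This bias can go in either direction.

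The point is not that a covariate list is incomplete, which could be left to the SAP. The protocol positively names a covariate that does not fit its own objective.

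**Working it through.** **1. The named covariates, by when they are fixed**

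| Covariate | Source | Timing | Fit for a total-effect model |
|---|---|---|---|
| Change in CIRS-G | Sample Size Calculation | After randomisation; possibly caused by vitamin D, per the text | No |
| Education | Sample Size Calculation | Before randomisation | Yes |
| Season | Sample Size Calculation | Not altered by treatment | Yes |
| Serum PTH, calcium | Sample Size Calculation | Not stated; measured at baseline, W12 and W24 | Baseline yes, on-treatment no |
| AD/RD stratum | Analyses | Before randomisation | Yes |

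For calcium, the description of the Intervention group says that vitamin D can act on calcium absorption, so an on-treatment value could be affected by treatment.

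**2. Which analysis would carry these covariates**

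A t-test or Mann-Whitney test has no covariates. The logistic and proportional hazards models are described as exploratory and are not methods for a continuous change score. ANCOVA is the only named method that takes covariates for such a score. The link from the covariable list to the ANCOVA is therefore a reasonable inference, not a statement in the text.

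**3. The plan's own figure, as a starting point**

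Inputs: "a variance of 25 (standard deviation estimated at 5"; "to detect a 3-point difference in change from baseline in the ADAS-cog"; two-sided alpha 5%; power 99%; 52 per group.

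- Two groups: n per group = 2 × (1.960 + 2.326)² × 5² / 3² = 102.1, rounded up to 103. The stated 52 does not reproduce.
- One sample against a fixed reference: n = ((1.960 + 2.326) × 5 / 3)² = 51.03, rounded up to 52. This gives the stated figure but is not the two-group comparison.
- Power at 52 per group for 3 points: Φ(3 / (5 × √(2/52)) − 1.960) = Φ(3.059 − 1.960) = 0.864 (0.858 with the t distribution).

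The sample size discrepancy is a separate matter, and the present point does not depend on it. What is needed here is that an unadjusted two-group test at 52 per arm has power of about 0.86.

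**4. What adjustment does**

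In a linear model without interaction, suppose treatment shifts the mediator by s (in SDs) and the within-arm slope of the outcome on the mediator is b. Then:

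adjusted contrast = total effect − s × b

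If b reflects only the causal path and f is the mediated share, s × b = f × total, so the adjusted contrast is (1 − f) × total. If b also contains association from unmeasured shared causes, the contrast moves further, up or down, even when f = 0. The variance of the treatment estimate is also multiplied by 1 + s²/4, because treatment and mediator are correlated: 1.0625 for s = 0.5 and 1.25 for s = 1. That raises the standard error by 3% or 12% before any gain from explained outcome variance.

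**5. Illustration**

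From the protocol: 52 per arm, a true difference of 3 points, within-arm SD 5. Assumed, because the documents give no values: f and s, and no shared causes. Power is from 4,000 simulated trials per row.

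| Mediated share f | (1 − f) × 3 | Simulated estimate | Power, s = 0.5 | Power, s = 1 |
|---|---|---|---|---|
| Mediator not in model | 3.0 | 2.98 | 0.85–0.86 | 0.85–0.86 |
| 10% | 2.70 | 2.68 | 0.75 | 0.67 |
| 25% | 2.25 | 2.23 | 0.63 | 0.52 |
| 50% | 1.50 | 1.48 | 0.44 | 0.28 |

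With f = 0 and no shared causes the expected estimate stays at 3.0.

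**The case against.** The strongest reply has four parts.

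- **The unadjusted comparison is intact.** The Analyses section plans a t-test or Mann-Whitney test on the change scores, and the sample size is framed as a plain two-group difference. That comparison preserves randomisation. This stands. A reader might infer that the trial's efficacy result or its overall power is compromised; the text does not support that, because the figures above describe only an adjusted model containing the mediator. The unadjusted test is not a full answer, though, since it is not named as the primary analysis ahead of the ANCOVA.
- **The ANCOVA's covariates are not listed.** The covariables are tied only to multivariate analyses, a word that the Analyses section also uses beside exploratory models. This stands as a limit on what can be claimed. Against it, nothing labels CIRS-G change as exploratory, and the covariables appear within the calculation for the ADAS-cog comparison.
- **PTH and calcium may be baseline values.** A reader might infer that these too are post-randomisation covariates. The text does not say so: both are measured at baseline as well as later, and the word for change is attached to comorbidity, not to them. What remains is a time point to be stated.
- **The magnitude is assumed.** It is. Nothing in the protocol indicates how far CIRS-G could move in 24 weeks, or whether any of the effect runs through it.

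None of this touches the core: the protocol names the change score as a covariable and describes it as a possible consequence of treatment that may affect the outcome.

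**Conclusion.** The concern holds for one named covariate, the change in CIRS-G. By the protocol's own wording it is a post-randomisation mediator, and an adjusted comparison of ADAS-cog change that includes it would not answer the primary objective. That such a model is the ANCOVA is inferred. For PTH and calcium the conclusion is narrower: the protocol should say that baseline values are meant.

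The size cannot be taken from the documents. The estimates in the table assume a linear model, no shared causes and the stated shares; the power figures also depend strongly on how far treatment moves the mediator. They show that even a modest mediated share would matter in the adjusted model, and nothing more.

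**What to change.** Add one sentence to the protocol or the SAP, before unblinding: adjusted efficacy models use only values measured before randomisation, namely the baseline score of the outcome, AD/RD stratum, education, season at inclusion, and baseline CIRS-G, PTH and calcium. Remove CIRS-G change from those models, and exclude any W12 or W24 PTH or calcium. If the indirect path is of interest, report it as a separately labelled exploratory mediation analysis with its assumptions stated. If the SAP does not already do so, the same edit can say whether the unadjusted test or the ANCOVA is primary.

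The cost is the wording. The sample size does not change. No new data are needed, because a CIRS-G change score already requires a baseline CIRS-G, and Table 1 already has PTH and calcium measured before inclusion.
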